## Abstract

**Background:**

More than 2.5 million people are admitted for surgery in Australia each year, and between 40 to 80% will experience moderate to high preoperative anxiety. Elevated levels of preoperative anxiety can increase the risk of postoperative complications such as pain, delayed wound healing, infection, prolonged recovery, and longer hospitalisation. Limited previous research on Virtual Reality (VR) indicates a positive impact on surgery-related anxiety and suggests that the intervention potentially leads to reduce postoperative complications.

**Objective:**

To evaluate the effectiveness of using VR technology for perioperative anxiety among adults undergoing elective surgery.

**Method:**

A two-group parallel randomised controlled trial (RCT) will be conducted, including 150 adult patients (aged 18 years and over) undergoing elective surgery and requiring an overnight stay at a major metropolitan hospital. Eligible participants will be screened for anxiety via the Amsterdam Preoperative Anxiety and Information score (APAIS). Those with moderate to severe anxiety will be randomly allocated to receive the VR session or usual care, in the preoperative holding area. Intervention participants will use a head-mounted VR device to watch and listen to a nature scene for 10 minutes.

**Study outcomes:**

The primary outcome is perioperative anxiety measured using the visual analogue scale for anxiety (VAS-A). Secondary outcomes include stress levels (measured by saliva cortisol level and heart rate), postoperative pain, patient satisfaction with perioperative care, hospital length of stay, and VR-associated adverse events.

**Conclusion:**

This study will help evaluate if a brief preoperative VR session can reduce perioperative anxiety for adult elective surgical patients.

**Trial registration:**

Australia and New Zealand Clinical Trials Registry (ANZCTR) ACTRN12620001350910.

**Supplementary Information:**

The online version contains supplementary material available at 10.1186/s13063-022-06908-3.

## Administrative information

Note: the numbers in curly brackets in this protocol refer to SPIRIT checklist item numbers. The order of the items has been modified to group similar items (see http://www.equator-network.org/reporting-guidelines/spirit-2013-statement-defining-standard-protocol-items-for-clinical-trials/).

## Background {6a}

Rates of anxiety tend to increase among patients who are scheduled for surgery, regardless of the surgery type. The prevalence of preoperative anxiety has been estimated by a number of studies worldwide [1–3]. A prospective study conducted in Austria, Canada, and Sri Lanka revealed that 45.3%, 89%, and 76.7% of surgical patients respectively experienced significant preoperative anxiety [1–3].

About 40 to 80% of adult surgical patients report experiencing anxiety triggered by different causes [4–6]. These include pain anticipation, loss of independence, separation from family, fear of the anaesthesia, fear of unfavourable diagnosis, changes in appearance, or the possibility of death [7, 8]. Most patients experience anxiety during the preoperative phase, and it is usually recognised as a normal patient response. The extent to which each patient manifests anxiety depends on many variables, such as age, gender, previous surgical experiences, educational status, type of surgery, current health status, and socioeconomic status [9]. Some patients, such as women or young patients, have high levels of preoperative anxiety [9, 10].

High or prolonged levels of preoperative anxiety lead to a number of negative consequences [7]. The most common postoperative complaint is postoperative pain [11, 12]. As a result, the need for postoperative pain medication increases, and this affects postoperative recovery [11, 12]. A study by Kavakci et al. [11] investigated the relationship between the level of preoperative anxiety and the pain level in the postoperative period, analgesic requirements, and the duration of hospital stay among adult patients (*n* = 103) who underwent ear, nose, and throat (ENT) surgery. There was a medium positive correlation between a patient’s anxiety level based on the Hospital Anxiety and Depression Scale, and their postoperative pain based on the visual analogue scale for pain (VAS-P) scores (*r* = 0.30, *p* < 0.002) [11]. In a recent study, preoperative anxiety and postoperative pain were examined among Chinese patients undergoing laparoscopic hysterectomy. Results show that patients with higher preoperative anxiety experience more postoperative pain [13].

As anxiety raises cortisol levels, preoperative anxiety has also been shown to delay wound healing, cause imbalanced fluid and electrolyte levels, and increase the risk of infection [14, 15]. In an experimental study, 24 healthy young men undergoing 4-mm punch biopsy were monitored for 21 days using ultrasound biomicroscopy to evaluate wound healing [16]. Self-reported stress levels were evaluated using the Perceived Stress Scale (PSS) self-report questionnaire. The results showed a significant negative correlation between speed of wound healing and the Perceived Stress Scale (PSS) scores (*r* = −.59; *p* < .01), indicating that slower wound healing was associated with higher perceived stress on the biopsy day. Cortisol levels were significantly increased for both groups (*F* = 14, 71, *p* < 0.01), but the total cortisol levels of the ‘slow healing’ group were significantly higher than those of the ‘quick healing’ group (significant group effect: *F* = 5.60, *p* < 0.05) [16].

Many strategies have been used to manage high levels of preoperative anxiety in both inpatient and outpatient settings. Pharmacological interventions including anxiolytic drugs such as midazolam, fentanyl, morphine, and ketamine are most commonly utilised [17]. Pharmacological treatments can lead to adverse effects such as breathing difficulties, drowsiness, interference with anaesthesia drugs, and prolonged recovery [18]. So non-pharmacological interventions including music, educational videos, psychological counselling, and social support are increasingly common [7, 9, 19–21].

Recently, there is growing interest in reducing preoperative anxiety through virtual reality (VR) technology. VR has been defined as ‘a computer-generated display that allows or compels the user (or users) to have a sense of being present in an environment other than the one they are actually in and to interact with that environment’ [22]. It has been proposed that this immersive technology can be used as a distraction tool to deflect patients’ attention away from their concerns regarding their upcoming surgery [23–26]. Previous studies have measured the effectiveness of using VR for perioperative anxiety in children. Four previous studies have focused on VR for reducing perioperative anxiety in adult patients undergoing surgical procedures [23–26].

These studies show that VR significantly reduced anxiety compared to control groups while increasing patient satisfaction and self-reported preparedness for surgery. The length of hospital stay and pain level showed no significant change between VR and control groups [23–26]. A limitation of these studies was the inclusion of all surgical patients regardless of their preoperative anxiety level. The other limitations of these studies include failure to report adverse VR symptoms, such as nausea, vomiting, headaches, or discomfort. Also, none of the RCTs had used biomarkers for stress levels as an objective measurement tool [23–26].

This study aims to evaluate the effectiveness of using VR technology for perioperative anxiety among adults undergoing elective surgery who experiencing moderate levels of anxiety. Secondary outcomes that will be evaluated include pain, stress, patient satisfaction with perioperative care, length of hospital stay, and VR-related adverse effects.

## Methods

### Study design and setting {8} {9}

A two-group parallel, single-centre, superiority, randomised controlled trial (RCT) with an allocation ratio of 1:1 will be conducted and reported in accordance with the CONSORT guidelines [27]. A total of 150 patients undergoing elective surgery will be randomised to the control (standard preoperative care) or intervention (standard preoperative care plus VR intervention) groups. The intervention will be delivered using the Oculus Quest 2 Virtual Reality Headset™ fitted with a smartphone (Fig. 1). This device has been chosen because it is the most advanced commercially available all-in-one VR device from Oculus, equipped with a highly immersive headset, two controllers, and integrated headphones. This study will be conducted in the surgical unit of a major Australian metropolitan hospital.

**Fig. 1 Fig1:**
[figure not shown]
Oculus Quest 2 Virtual Reality Headset™

### Study aim {7}

The aim of this study is to evaluate the effectiveness of using VR technology for perioperative anxiety among adults undergoing elective surgery.

### Hypothesis {6b}

Compared with standard care, a VR intervention delivered during the preoperative period will significantly reduce perioperative anxiety in adult elective surgical patients by 20 points on a 100-point visual analogue scale for anxiety (VAS-A).

### Recruitment {15} {26a}

The primary investigator will consult the hospital’s admission team to review the surgical list and identify potential participants. The potential participants will be asked to participate in the study via the hospital confirmation SMS providing them details of their surgery. They will be provided with a participant information statement and consent form via a link in the SMS. Potential participants will be requested to return their signed consent prior to their day of surgery if they are interested in participating in the study.

### Inclusion and exclusion criteria {10}

Patients will be eligible for inclusion if they are 18 years old and over, scheduled for elective surgery, can understand English, and can follow instructions. Patients will be excluded if they are scheduled for day surgery, have a history of seizures or motion sickness, have visual impairment, or are unable to complete a self-reported questionnaire.

### Screening

Patients who meet the above inclusion criteria will be screened for their anxiety level using a validated tool—the Amsterdam Preoperative Anxiety and Information score (APAIS) [28, 29]—on the day of their surgery in the preoperative holding area. Patients with moderate to high preoperative anxiety levels—described by preoperative anxiety score ≥11 [30]—will be included in the study and randomised to the intervention or control group.

The APAIS is a rapid and clinically practical assessment tool developed by Nelly Moerman and previously validated against other scales to evaluate patients’ preoperative anxiety with good sensitivity and strong specificity for clinically significant anxiety [28, 29]. It consists of six questions in total. Each question is rated on a 5-point Likert scale from “not at all” to “extremely”. The sum of scores from questions 1, 2, 4, and 5 show the anxiety level, while the sum of scores from questions 3 and 6 show the level of information required by each individual. A patient with a score of 11 or more (scoring range from 4 to 20) on the anxiety scale experiences anxiety and requires further intervention [28, 29, 31]. On the need for information scale, patients scoring 2–4 are categorised as having minimal or no need for information, patients scoring 5–7 are categorised as having an average need for information, and patients scoring 8–10 are considered as having high need for information [28, 31].

### Randomisation and allocation concealment {16a} {16b}{16c}

Participants will be randomly allocated to intervention or control via block randomisation on a 1:1 ratio (control: intervention) using a computer-generated random number sequence created by an independent statistician. In addition, randomisation will be stratified by surgery type (i.e. ENT surgery, general surgery, neurosurgery, maxillofacial surgery, urology surgery, vascular surgery, orthopaedics, and other surgeries). Electronic allocation via an online platform (the REDCap™ randomisation module) will be used to conceal the treatment allocation from the researcher until they have been deemed eligible and screened.

### Blinding {17b}

The Research Assistant involved in outcome data collection will be blinded to group allocation, as will the statistician who will conduct the data analysis. Clinicians (nurses, doctors, and other health providers) will not be told who is participating in the study nor their group allocation; however, it is acknowledged that it is not possible to prevent participants from sharing this information with them.

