### Virtual reality intervention {11a}

The participants will be asked to wear the VR headset for 10 min, which has been suggested in the literature to be the optimal time frame for VR without adverse side effects [32, 33]. The participants will be seated in the preoperative holding area while immersed in a VR. The preoperative holding area has been selected for administration of the intervention because evidence suggests preoperative anxiety levels among adult surgical patients peak in the preoperative holding area [34]. The VR will be used for relaxation purposes with nine natural scenes combined with natural sounds and music, for the participant to select from: blue moon, red savanna, blue ocean, green meadows, black beginning, white winter, blue deep, red fall, and the orange sunset (Fig. 2). The participant’s face and forehead will be cleaned using skin-friendly antibacterial cleaning wipes before using the VR device. Disposable hygiene covers will be used to protect the VR device. The researcher will provide the intervention and monitor the participant for adverse side effects such as headache, nausea, vomiting, sweating, fatigue, drowsiness, disorientation, and apathy throughout the session [33].

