### Criteria for discontinuing the trial in an individual {11b}

The researchers will monitor the participants continuously for side effects. If a side effect occurs, the VR session will be ceased immediately, and a treating medical team will be consulted. Also, there may be a risk of exacerbating the participant’s anxiety level associated with using a survey to assess anxiety. If this is the case, participants to be instructed to stop the survey and appropriate support will be provided by the researcher or medical team.

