### Ethical issues {22}

The study, including the participant information and consent form, has been reviewed and approved by the Royal Brisbane & Women’s Hospital Human Research Ethics Committee (RBWH HREC) (HREC/2021/QRBW/74417). Participation is voluntary and decline to participate will involve no penalty or loss of benefits to which the participant is otherwise entitled, and participants may discontinue participation at any time without comment or penalty.

There are possible risks (side effects) associated with the VR intervention ^(38).^ Although rare, side effects may include headache, nausea, vomiting, sweating, fatigue, drowsiness, disorientation, and apathy [33]. Any adverse events that arise, whether related to the study intervention or not, will in the first instance be reported to the clinical nurse manager and to the researchers, who will then submit a report of the event to the HREC.

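### Every adverse event is promised to be reported, but no systematic collection is stated after T2 or in the control arm, and clinicians who might fill the gap are not told who is participating

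*Protocol article*

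**What the plan says.** Four parts of the protocol article bear on this point.

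- **Reporting promise (Ethical issues {22}).** "Any adverse events that arise, whether related to the study intervention or not, will in the first instance be reported to the clinical nurse manager". The researchers are named as recipients too, and they pass the report on to the ethics committee. The promise is not limited by arm, time or cause. It does not say who detects or reports an event.
- **Monitoring.** Under Virtual reality intervention {11a}, the researcher who delivers the session is to "monitor the participant for adverse side effects such as headache, nausea, vomiting, sweating, fatigue, drowsiness, disorientation, and apathy throughout the session". Criteria for discontinuing the trial in an individual {11b} says: "The researchers will monitor the participants continuously for side effects". It continues: "If a side effect occurs, the VR session will be ceased immediately, and a treating medical team will be consulted".
- **Adverse-effect outcome (Secondary outcomes; Table 1).** VR adverse effects are defined without restriction to one time point. The instrument, the VRSQ, is completed once, at T2, by the intervention group only. Table 1 marks this outcome at t2 and nowhere else.
- **Non-disclosure (Blinding {17b}).** "Clinicians (nurses, doctors, and other health providers) will not be told who is participating in the study nor their group allocation". The only qualification is that "it is acknowledged that it is not possible to prevent participants from sharing this information with them".

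**The concern.** The Blinding section goes further than masking the arm, because it withholds participation itself. After the patient leaves the holding area, much of what happens in theatre, in recovery and on the ward is seen by clinicians. If they do not know that a patient is in a trial, they have no stated reason to pass an event to the researchers. The trial team's own stated collection has by then ended.

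Two things are at stake. The first is whether the undertaking on reporting to the ethics committee can be kept by the procedures described. The second is whether any count of adverse events can be compared between arms. The Background criticises earlier VR trials for not reporting symptoms such as nausea, vomiting and headache. Several of the symptoms listed for monitoring could also arise from surgery or anaesthesia, so a later symptom in the VR arm is hard to interpret unless controls are asked the same question.

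**Working it through.** The document gives no figure to reproduce and no adverse-event rates. The check sets the promised coverage beside the collection stated for each period and arm.

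| Period | Intervention arm (75 planned) | Control arm (75 planned) | Source |
|---|---|---|---|
| During the 10-minute session | Monitoring by the researcher | None stated | Virtual reality intervention {11a} |
| After the session, up to T2 | VRSQ, requested by the researcher | None stated | Secondary outcomes; Table 1 |
| T3 (1 h, post-anaesthesia care unit) | Anxiety, heart rate, pain; no adverse-event item | Same | Primary outcome; Secondary outcomes |
| T4 (24 h, before discharge) | Satisfaction questionnaire; no adverse-event item | Same | Secondary outcomes |
| Record review | Listed items do not include adverse events | Same | Other data |

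1. **Coverage by arm.** Stated adverse-event collection reaches 75 of the 150 planned participants, and only up to T2. The other 150 − 75 = 75, all controls, have none. The section on discontinuation does provide support if the survey itself worsens anxiety, and this could apply to controls, but it describes support and not recording.

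2. **Coverage by time.** After T2 no participant in either arm has a stated adverse-event question or item. The unrestricted time window in the outcome definition is therefore served by a single administration.

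3. **Clinicians as a substitute.** They are not told who participates. The one stated way they may learn of it is that a participant mentions it, which is not a reporting route.

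4. **The same tension in the other direction.** Reporting an event to the clinical nurse manager, or consulting the treating team about a VR side effect, tells clinical staff that the patient is a participant. In the second case it also reveals the arm. The Blinding section states no exception for this.

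5. **Symptoms disclosed at T2.** The VRSQ is completed after the session and immediately before surgery. The section on discontinuation links a side effect both to ending the session and to consulting the treating team. The article does not say how a symptom first disclosed on the VRSQ relates to that consultation or to the non-disclosure rule.

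**The case against.** The strongest reply is that much of this is unstated detail and not contradiction, and a good part of that reply stands.

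- A reader might infer that reporting depends on clinicians once the session ends, or that later events cannot reach the researchers or the ethics committee. The document supports neither. The Ethical issues section names no reporter and makes the researchers direct recipients. Contacts at T3 and T4, the researcher's use of the health record, and participants speaking for themselves could all bring events to light. These routes are incidental, not systematic.
- A reader might infer that symptoms arising after the headset is removed are missed. Up to T2 they are not: the VRSQ is requested by the researcher, not by a clinician. The gap in the intervention arm begins after T2.
- A reader might see a conflict between "The researchers will monitor the participants continuously for side effects" and monitoring "disorientation, and apathy throughout the session". The sentence that follows the first is about stopping the session, so both can describe continuous watching while the headset is on.
- A reader might infer that a symptom found on the VRSQ has no route to the treating team. The text ties consultation to the occurrence of a side effect, and ending the session is a parallel step. The relation is not spelled out, but it is not excluded.
- The sections can be followed together. Non-disclosure is a default, and nothing forbids telling clinicians when an event occurs.
- A journal article commonly leaves forms and operational safety procedures to the full protocol, which is not shown.

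The last reply does not dispose of the point. The concern does not rest on missing forms. It rests on what the article does state: an unrestricted promise, an outcome not limited in time but measured once in one arm, and a rule that withholds participation from clinicians. Following those statements as written gives an uneven record.

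**Conclusion.** The point holds in a limited form. No stated route systematically captures adverse events after T2, or adverse events in the control arm at any time, and clinicians who are not told of participation cannot be relied on to supply them. The adverse-event record would be incomplete and not comparable between arms, and it would fall short of what the Ethical issues and Secondary outcomes sections promise.

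The size can be stated only as coverage: no stated collection in the planned 75 controls, and none after T2 in all 150. How many events would be missed cannot be derived from the document. The conclusion assumes that the article's lists of measurements at T3, at T4 and from the health record are complete; a fuller protocol could narrow the gap. The consequence is modest. The intervention is a single 10-minute session, and the analysis of the primary anxiety outcome is unaffected. It is a worthwhile, cheap improvement and not a flaw that invalidates the trial.

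**What to change.** 1. In Blinding {17b}, limit non-disclosure to group allocation, so that clinicians can know that a patient is participating and can report events to the researchers.
2. Ask one identical adverse-event question in both arms at the existing T3 and T4 contacts. Word it without reference to VR, so that the Research Assistant stays blinded. Name who asks it at T4, since the article does not say who gives the satisfaction questionnaire.
3. If neither change is wanted, narrow the promise in Ethical issues {22} and the time window in Secondary outcomes to what is actually collected.
4. Reconcile Blinding {17b}, Virtual reality intervention {11a}, Criteria for discontinuing {11b}, Secondary outcomes and Ethical issues {22} on what happens to a symptom disclosed at T2. The clinical route is for the investigators and the treating team to decide; the sections need only agree.

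The cost is protocol wording, a means of letting clinicians know of participation, and one question at two existing contacts. The small downside is that clinicians learn that a patient is in a trial, though not the arm. As this changes the protocol, the revision goes to the Ethics Committee, as the article's section on amendments already provides.
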